### Procedures

Baseline and 24-week assessments are being collected remotely via password protected online surveys using RedCap™ software. Data will be deidentified and downloaded into Microsoft® Office Excel software and stored in password protected computer files on the university server. All authors will have access to the final trial dataset. The most symptomatic knee at the time of enrolment is the focus of evaluation. In cases where both knees are equally symptomatic and eligible, the right knee is deemed the study knee. All participants provide informed consent to participate via online consent forms, prior to completing baseline assessments.

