##### My Knee Exercise website

The website contains a home page and four sections that provide educational information, guidance to increase general physical activity, a 24-week home-based lower limb strengthening exercise program and resources to support exercise (e.g. printable logbooks). The website was constructed by the authors who received website development training from a web-designer. The website was developed in accordance with recommendations outlined by The Health on the Net Foundation’s Code of Conduct [52]. This code provides an ethical standard for the reliability of internet-delivered medical and health information. Three people with knee OA provided input on the website prototype regarding design, content and usability which informed the finalised website. The literacy demands of all written material in the website was evaluated with recommended [53] and previously used [54, 55] online readability software (Readable.io, Added Bytes, Ltd., Sussex, UK) as suitable for individuals with a 5th-grade reading ability. This is in accordance with the recommended reading level for consumer healthcare information of no greater than 6th–8th grade [56, 57]. Material within the website was specifically developed for this study. The website is not tailored to each participant. All participants receive the same standardised website. Website sections are discussed in detail below.

Home Page: The website home page includes a video tutorial called “Start here.” This tutorial explains and models use of each section of the website, encourages participants to start the strengthening exercise as soon as possible and explains the SMS exercise support. The home page also contains links to the four sections of the website plus links to ‘contact us’ and ‘about us’ information.

My Knee Education: This section contains written information about living with knee OA, knee OA treatments, exercise as treatment for knee OA, recommended exercise for knee OA and managing exercise pain. Written information is supported by video interviews of people with knee OA and OA experts. Participants are directed to view the written and audio-visual material prior to commencing the strengthening exercise program prescribed within the ‘My Knee Strength’ section of the website. Participants can download copies of all written information.

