My Knee Strength: This section describes a 24-week, self-directed, home-based, lower limb strengthening exercise program. Over 24-weeks, participants are instructed to complete three, eight-week exercise programs, completed in succession. The exercise protocols were chosen based on those demonstrated to reduce pain and improve physical function in people with knee OA when prescribed by a physiotherapist [42, 58]. Participants receive a SMS at week one to prompt commencement of exercise program one and a SMS at week eight and week 16 to encourage use of the website and progression to exercise program two and three, respectively. Program one and two contain five exercises and program three contains six exercises. Exercises in each program target the hip, knee and ankle, and include for example seated knee extension, walk squats, hip abduction and calf raises. Two to three new exercises replace other exercises in each program to add variety and increase the exercise challenge. Exercise dosage, in accordance with recommendations for muscle hypertrophy [59], is: 10 repetitions; three sets with 2 min rest between each set; three times a week; at an exercise intensity of hard [4, 5] in program one and very hard [6, 7] in program two and three, as rated on an 11-point scale of Rated Perceived Exertion (RPE) for strength training [60]. Intensity is increased for each exercise by adding ankle weights and/or changing body position. In line with a pragmatic approach, participants are encouraged to purchase their own ankle weights to progress their exercises throughout the 24-week intervention. Each exercise session is estimated to be 20–30 min duration. Written instructions are provided for each exercise as well as photographic and video demonstrations. Participants can download and print a copy of each exercise program. Downloadable exercise logbooks for each program are also provided. Participants are encouraged, but not mandated, to use the log books to record their weekly exercise practice. ‘My Knee Strength’ also contains suggestions of what and where to purchase exercise equipment to progress the exercises, tips for starting and sticking to exercise, and provides details about the SMS exercise adherence program.

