#### Process measures

A range of process measures are assessed at 24-weeks, unless indicated otherwise.

*Exercise importance (baseline and 24-weeks)*: Participants will be asked the question “How important is it to you to do regular exercise to manage your knee condition?” Responses are collected on a 7-point scale with terminal descriptors 1 = ‘not at all important’ and 7 = ‘extremely important’. Scores range from 1 to 7, with higher scores indicating higher importance.

*Self-reported number of exercise days in the previous week:* Participants are asked “In the past week, how many days did you participate in exercise for your knee condition?” Scores range from 0 to 7.

*Adherence to prescribed home exercise:* Exercise Adherence Rating Scale (EARS) Section B is being used to measure adherence to prescribed home exercise [69]. This is a 6-item measure. Responses are collected on a 5-point scale. Scores range from 0 to 24 with higher score indicating better adherence.

*Perceived usefulness of study website*: Participants are asked to report their level of agreement with the statement “I thought the website I accessed as part of the study was useful in helping me manage my painful knee”. Responses will be collected on a 7-point scale with terminal descriptors 1 = ‘strongly disagree’ and 2 = ‘strongly agree’. Scores range from 1 to 7 with higher scores indicating higher perceived usefulness.

*Perceived usefulness of SMS exercise adherence support (intervention only)*: Participants are asked to report their level of agreement with the statement “I thought the mobile phone text messages I received were useful in helping me manage my painful knee”. Responses will be collected on a 7-point scale with terminal descriptors 1 = ‘strongly disagree’ and 2 = ‘strongly agree’. Scores range from 1 to 7 with higher scores indicating higher perceived usefulness.

*SMS frequency feedback (intervention only)*: Participants agreement with the statement “The number of text messages I received over the past 6 months was the right amount for me.” Responses will be collected on a 7-point scale with terminal descriptors 1 = ‘strongly disagree’ and 2 = ‘strongly agree’. Scores range from 1 to 7 with higher scores indicating higher agreement. Participants who select ≥3 will be asked ‘Did you receive too many or too few?’ with response collected via 1 = ‘too few’ or 2 = ‘too many’.

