*Website access:* Participants are asked to estimate how many times they accessed their study website in: i) the first month of the study, and ii) month five of the study. Responses are collected in an open numerical field box.

*Exercise equipment purchased:* Participants will be asked if they purchased any exercise equipment to help them with their knee exercise. Participants who select ‘yes’ will be asked to estimate the cost of the equipment purchased in an open numerical field box.

*Website and SMS program data:* Interaction data will be collected from both websites and the SMS program such as website logins and SMS program ‘opt-outs’.

*Adverse events*: Any problem that participants believe was caused by the information received as part of the study and required them to seek treatment/take medications, and/or interfered with function for two or more days are recorded via questionnaire.

*Co-interventions:* Medications and other treatments for knee OA are recorded at 24 weeks using a custom-developed survey. This survey records the frequency of use of a range of pain and arthritis medications and co-interventions over the past 6 months.

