#### Monitoring

Monthly meetings are held between the trial coordinator and lead investigators to review recruitment, trial progress, monitor adverse events and any other issues relating to the trial.

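### Adverse events are recorded only if the participant attributes them to the study information, and no described route takes events before week 24 to the monthly meetings

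*Protocol article*

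**What the plan says.** Under Process measures, the protocol article sets two conditions for an adverse event. The first is causal: "Any problem that participants believe was caused by the information received as part of the study". The second concerns consequences: the problem "required them to seek treatment/take medications, and/or interfered with function for two or more days are recorded via questionnaire".

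The same section opens with a timing rule: "A range of process measures are assessed at 24-weeks, unless indicated otherwise". The entry on exercise importance marks an exception to that rule; the adverse-event entry marks none. Procedures describes only two survey points: "Baseline and 24-week assessments are being collected remotely via password protected online surveys".

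Monitoring says: "Monthly meetings are held between the trial coordinator and lead investigators to review recruitment, trial progress, monitor adverse events" and other trial matters.

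The arms differ in what they are given. Of the strength section of the intervention website the article says: "This section describes a 24-week, self-directed, home-based, lower limb strengthening exercise program". The control website has no exercise program, only general exercise and physical activity recommendations to be taken up at the participant's discretion.

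**The concern.** A problem that the participant does not link to the study is never recorded, whatever its consequences. Whether it is linked depends on what the participant was given. Someone prescribed a specific strengthening program has an obvious candidate cause for a knee flare; someone given general recommendations has a weaker one. Randomisation balances the underlying events between arms, but it does not balance a filter that acts after allocation and may depend on it.

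Timing adds a second difficulty. If the questionnaire is asked once, at 24 weeks, early events are subject to about half a year of recall, and those who do not return the survey contribute nothing. The monthly meetings are said to monitor adverse events, but the article does not say what reaches them while a participant is still in follow-up.

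At stake is the safety statement for an unsupervised home program. Participants are at least 45 years old, and some with a recent fall, housebound status or a failed pre-exercise screen may enter after clearance by a general practitioner. No efficacy result, sample size or power figure depends on this point.

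**Working it through.** The article states no adverse-event rate, so there is no such figure to reproduce. The check sets the passages side by side and then shows by arithmetic what the definition can do.

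**1. Timing against monitoring**
- Process measures: 24 weeks by default, no exception for adverse events.
- Procedures: surveys at baseline and 24 weeks only.
- Monitoring: adverse events monitored monthly.

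A problem in week 1 is first asked about 24 − 1 = 23 weeks later, after about five monthly meetings. Until the first participants reach 24 weeks, the described questionnaire supplies the meetings with nothing.

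**2. Participants without a questionnaire**
- Inputs (Sample size calculation): 206 in total, 103 per arm, 15% loss to follow-up. The size reproduces: 87 per arm for an effect of 0.40 with a pre-post correlation of 0.35, two-sided 0.05 and 80% power; 87 / 0.85 = 102.4, rounded up to 103 per arm, or 206.
- No 24-week survey: 206 × 0.15 = 30.9, about 31 in total; 103 × 0.15 = 15.45, about 15 per arm.

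**3. What attribution can do to the count**

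Expected count per arm = 103 × p × 0.85 × c, where p is the true proportion with a qualifying problem, 0.85 is the proportion returning the survey, and c is the share of those problems both recalled and attributed to the study. Neither p nor c is given in the document. All values of p and c are assumptions, and loss is taken as unrelated to harm.

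| p | True number (103 × p) | c = 1.00 | c = 0.75 | c = 0.50 |
|---|---|---|---|---|
| 5% | 5.2 | 4.4 | 3.3 | 2.2 |
| 10% | 10.3 | 8.8 | 6.6 | 4.4 |
| 20% | 20.6 | 17.5 | 13.1 | 8.8 |

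Two pairs from this table show why the direction is open:
- Equal true rates of 10%, with c = 0.75 in one arm and 0.50 in the other: 6.6 against 4.4, a ratio of 0.75 / 0.50 = 1.5 where the truth is 1.
- True rates of 20% and 10%, with c = 0.50 and 1.00 respectively: 8.8 against 8.8, so a true ratio of 2 appears as 1.

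The first creates a difference and the second hides one. The document gives no basis for choosing between them.

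**The case against.** **The wording covers exercise harms.** One might infer that asking about information leaves out harm from doing the exercises. It does not: the program is delivered as website content, so a problem from following it falls within information received. Neutral wording also suits a trial in which participants are blinded to group. This stands.

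**Bias is not demonstrated.** A reader might infer that harms are under-counted or that the safety result is biased downwards. Readier attribution in the exercise arm would exaggerate the contrast against the intervention, and controls can also attribute problems to the recommendations they receive. This stands: the comparison is hard to interpret, but no direction or size is shown.

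**There is no proven contradiction, and the meetings are not empty.** Nothing says the questionnaire is the only source for the monthly meetings. If enrolment is staggered, 24-week surveys would arrive in successive months. The intervention site offers a contact route: "The home page also contains links to the four sections of the website plus links to ‘contact us’ and ‘about us’ information". Collection at 24 weeks only is inferred from a section default; the schedule in Table 2 is not shown, and a journal article may leave unsolicited reporting to the full protocol. This stands against a claim of strict contradiction. It leaves the need to say how earlier events reach the meetings, since the contact link is not tied to adverse events.

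**Loss is not the same as harm.** The 15% is a planning allowance. Someone who stops exercising or opts out of the messages can still return the survey, so one cannot infer that everyone who stopped because of a problem is lost.

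**Other data exist.** Pain, function, perceived global change, medications and co-interventions are collected in both arms without attribution to the study. They show worsening but do not replace a record of adverse events.

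None of these points removes the causal filter, which the article states outright.

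**Conclusion.** The point holds in limited form. The case definition makes recording depend on the participant's own attribution, and the arms differ in what they have to attribute a problem to. Neither the absolute count nor a between-arm comparison from this item is cleanly interpretable. The article sets out no specific harms analysis, but this item is the only adverse-event record it describes, so any reported rate or contrast would draw on it.

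The size cannot be fixed from the document. The counts in the working rest on assumed rates and attribution shares. The only figure tied to the plan's own numbers is the roughly 31 of 206 participants without a 24-week questionnaire, and that assumes the planned loss occurs.

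On timing, the Process measures and Monitoring sections need to be reconciled, subject to Table 2 and the full protocol, which are not shown. This is an inexpensive improvement to the safety information, with no bearing on the efficacy analysis.

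**What to change.** 1. Keep the existing item, so that surveys already returned stay comparable.
2. Add to the 24-week survey, identically in both arms, one item on any new or worsened problem that meets the existing consequence criteria, whatever its perceived cause.
3. Add a separate item on whether the participant thinks the problem was related to the study. The attributed subset can then still be reported.
4. Attempt both new items in participants who do not complete the survey.
5. Base any between-arm comparison on the all-cause 24-week item only. Use unsolicited reports for monitoring and not for the comparison: the continuing message exchange and the contact link are described only for the intervention arm, so counting events from them would ascertain the arms unequally.
6. State in Monitoring how and when events before 24 weeks reach the monthly meeting, and make this consistent with Process measures.

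The cost is two survey items, some follow-up of non-completers and a sentence or two of protocol text. More unrelated events will be recorded. As recruitment is under way, participants who have already completed the survey will have only the existing item, and reports should give the number who answered each version.

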### Data analysis, monitoring and auditing

#### Sample size calculation

The sample size is based on detecting an effect size of 0.40 for the two primary outcomes of pain and WOMAC physical function. According to Cohen [70], an effect size of 0.40 represents a small to moderate difference between groups. This effect size was chosen based on mean effect sizes for exercise treatment in people with knee osteoarthritis. A meta-analysis of 44 clinical trials investigating land-based exercise showed effect sizes of 0.49 for pain and 0.52 for physical function [9]. As the current trial includes unsupervised exercise, which we believe may result in smaller effects, we powered the trial to detect a more conservative effect size of 0.40 for both primary outcomes. Thus, to achieve 80% power and 0.05 two-sided significance level, with a correlation between pre- and post-measurements of 0.35 for pain and function, and accounting for 15% loss to follow up [42, 58], we require 103 participants per arm, for a total of 206 participants. Assuming between-participant standard deviations of 2.3 for pain and 11.7 for WOMAC physical function based on our previous research [58] and a pre-post correlation of 0.35, this sample size of 206 participants will provide us with > 99% power to detect a minimal clinically important difference in pain of 1.8 units [71] and 95% power to detect a minimal clinically important difference in function of 6 WOMAC units [72].

#### Data analysis

Analyses comparing the two groups will be performed by the statistician in a blinded fashion using all available data from all randomised participants according to the intention-to-treat principle. Should the amount of missing data for an outcome be greater than 5%, multiple imputation will be conducted, and the method reported. The primary analysis will analyse the multiply imputed datasets. Demographic and baseline characteristics of participants will be summarised as appropriate (means and standard deviations for continuous variables that appear to be distributed approximately symmetrically, medians and interquartile ranges for other continuous variables, counts and percentages for categorical variables) and will be inspected to assess baseline comparability of treatment groups. For continuous outcomes, differences will be compared between groups in either change (baseline minus follow up) or at 24 weeks using linear regression models adjusted for baseline levels of these outcomes. Model assumptions will be assessed using standard diagnostic plots. We will also calculate the proportion of participants in each group that show an improvement that reaches or exceeds the minimal clinically important difference in NRS pain (≥1.8 units) and in WOMAC function (≥6 units). For this and other binary outcomes, differences between groups will be compared using relative risks, calculated from logistic regression models.

#### Monitoring

Monthly meetings are held between the trial coordinator and lead investigators to review recruitment, trial progress, monitor adverse events and any other issues relating to the trial.

### Dissemination plans

Trial findings will be disseminated at conferences, published in a peer-reviewed journal and a lay summary of findings provided to all participants. Findings will also be dissemination through research networks including the Centre for Health, Exercise and Sports Medicine, and the National Health and Medical Research Council Centre for Research Excellence in Translational Research in Musculoskeletal Pain. We anticipate making the ‘My Knee Exercise’ website available for the general population to access.

## Discussion

This RCT is investigating if a digitally delivered intervention that combines "My Knee Exercise’, a website containing knee OA and exercise education, guidance to increase general physical activity, and prescribes a 24-week home-based lower limb strengthening program with a behaviour change SMS exercise adherence program can improve knee pain and physical function at 24-weeks when compared to OA and exercise education alone. If effective, this combined intervention will be an easily scalable intervention with the potential to increase access to exercise programs for the treatment of knee OA. This intervention could be easily disseminated by primary care doctors and health professionals as a first- line intervention in a stepped care approach, provided by health insurers for their members and/or linked to currently available Internet delivered OA consumer resources.

## Data Availability

The SMS programs behaviour change message library will be available by request on a case-by-case basis at the discretion of the corresponding author.

## Abbreviations

BCT: Behaviour change technique
BCW: Behaviour Change Wheel
COM-B: Capability, Opportunity and Motivation model of behaviour
OA: Osteoarthritis
SMS: Short Messaging Service
TDF: Theoretical Domains Framework
